### Ethical Considerations

The institutional review board at the Pennsylvania State University approved all study procedures (#00021945). Participants provided informed consent before completing the baseline and daily diaries. Study data are deidentified. Participants could earn up to US $67 via an e-gift card for full participation in the study. Specifically, participants were compensated US $10 for the baseline survey, US $0.50/daily survey, a US $10 bonus if they completed 70+ of the 84 surveys, and US $5 for completing a brief exit survey.

## Results

Recruitment invitations were sent via direct email to 411 individuals. Of these, 92 (22%) completed the consent form, completed the baseline survey, and were randomized to either the EMA group or the EMA+DD group. Among these individuals, 91 (99%) ultimately participated in the EMA survey (ie, provided data at 1 or more EMA prompt), thus determining our final sample size. Data were collected during March and April 2023.

Participants were predominantly White (92%), non-Hispanic (89%), and female (67%), with a mean age of 20.3 (SD 1.18) years. Among the 91 participants, 43 (47%) were randomized to the EMA group and 48 (53%) were randomized to the EMA+DD group. Overall study compliance was very good, with a mean of 64.3 (14.6) out of 84 (76.5%) prompts completed, resulting in a total of 5896 (out of a possible 7644) person-moments of data.

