## Methods

### Participants and Trial Design

Participants were drawn from a sample of undergraduate college students at a large public university who previously participated in a large, campus-wide cross-sectional survey in Spring 2023 and agreed to be contacted for future research. Participants who indicated past-month alcohol use or lifetime marijuana, hashish, or Δ-8-tetrahydrocannabinol (THC) use or some combination thereof were sent an email inviting them to participate in this study. Individuals interested in participating contacted the study team for more information or moved directly to the screener questionnaire using unique REDCap (Research Electronic Data Capture; Vanderbilt University) survey links provided in their emails.

Individuals were eligible to continue into the study if their responses to the screener questionnaire indicated that they were 18-25 years of age, used alcohol and cannabis in the past 30 days, and used an iPhone with an iOS version of 12 or more recent. The iPhone eligibility requirement was added to overcome technical challenges and additional confounding elements related to variations in how REDCap surveys and visual messages are displayed in iOS versus Android systems. Previous work by the study team has shown that students in the current institution are overwhelmingly iPhone users.

Eligible participants who consented to participate in this study were randomized into either the EMA group or the EMA+DD group and directed to the baseline survey. The randomization was performed automatically such that each participant had a 50% chance of being assigned to either of the 2 groups. The team planned to collect data from at least 40 individuals in each study condition. Study team members were able to see participants’ group assignment but had no contact with participants at any time to avoid introducing interview bias. After completing the baseline survey, participants were automatically enrolled in the 21-day portion of the study, with day 1 starting on the first Thursday after baseline completion. During the 21-day portion of the study, the participants received text-based prompts with a personalized REDCap link to a web survey.

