### Study Implementation

The entirety of the study was conducted in REDCap, which is a free survey platform that allows researchers to create and manage surveys to collect data securely. The complex study was designed and implemented in a way that was fully automated.

Specifically, we created a project consisting of multiple surveys: a screener, a baseline survey, 4 momentary surveys (1 for each time of day: 11 AM, 2 PM, 5 PM, and 8 PM) for the EMA portion of the study, and an exit survey. Surveys were used to store participants’ contact information separately from the rest of the data. These surveys were uploaded by the research team for all potential participants. This triggered the automated survey invitations for these individuals to go out at a scheduled date and time. At each prompt, these automated invitations provided unique participant links to the screener survey.

The screener survey contained the consent form, as well as several eligibility-related questions. Once a participant clicked on the link and completed the screener, they were told whether they were eligible to continue. The survey ended for participants who were not eligible to continue, but they were provided with study team contact information if they had further questions.

Participants who were eligible after the screener survey were automatically forwarded to the baseline survey. After completing the baseline survey, each participant was redirected to a server maintained by the institution’s survey research center. This server randomly assigned each participant to the EMA or the EMA+DD condition and scheduled all 84 prompt invitations via texts using Twilio’s Multimedia Messaging service. For the EMA group, all 84 invitations would simply include the text “It’s time to complete your next survey:” with a link to the EMA survey in REDCap corresponding to that time of day.

For the EMA+DD group, on each of the 21 study days, the server would randomly select 1 of 4 prompts at which to deliver the DD. At the other 3 prompts during that day, participants would receive the standard message that was used for all prompts in the EMA group. Just before each prompt, if a participant was randomly determined to receive a DD at that prompt, the server used JavaScript libraries to calculate the compliance data for each participant and then generated a visual image showing their progress to date in the study, to be delivered at that prompt.

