### Outcome Measures

#### Primary Outcomes

This study focused on 2 objective measures of compliance and a set of quantitative and qualitative measures of subjective experiences. Primary outcomes included the following:

Overall compliance: overall compliance was derived from a moment-level binary measure of compliance (ie, an indicator of whether the participant completed the survey within 60 minutes of a particular prompt), summed across 84 prompts within an individual. This was used to address the question: “Did individuals who received a daily DD complete a greater number of surveys, on average, compared to those who did not?”Average time of survey response: average time was derived from the length of time between the survey prompt and survey completion (among completed surveys), averaged across up to 84 prompts. This outcome was used to address the question: “Did participants who received the DD complete surveys more quickly, on average, compared to those who did not?”Subjective experiences of the study protocol: subjective experiences were assessed in the exit survey and were compared across groups. This comparison relied on both quantitative and qualitative measures of experiences.

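### The final sample omits the one randomised participant who answered no prompt, so inclusion depends on the primary completion count itself

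*Protocol article*

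**What the plan says.** The Results section of the protocol article gives the number randomised: "92 (22%) completed the consent form, completed the baseline survey, and were randomized to either the EMA group or the EMA+DD group". It then sets the sample: "91 (99%) ultimately participated in the EMA survey (ie, provided data at 1 or more EMA prompt), thus determining our final sample size". The arm sizes are given for that reduced sample: "43 (47%) were randomized to the EMA group and 48 (53%) were randomized to the EMA+DD group".

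Under Primary Outcomes, overall compliance is built from a yes/no measure at each prompt, "an indicator of whether the participant completed the survey within 60 minutes of a particular prompt), summed across 84 prompts within an individual". The second primary outcome, average response time, is defined only over surveys that were completed. The third, subjective experience, comes from the exit survey.

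Under Study Implementation, prompts do not depend on any later action by the participant: "This server randomly assigned each participant to the EMA or the EMA+DD condition and scheduled all 84 prompt invitations via texts".

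On a side matter, Participants and Trial Design says that eligible people "were randomized into either the EMA group or the EMA+DD group and directed to the baseline survey", whereas Study Implementation puts the baseline survey first: "After completing the baseline survey, each participant was redirected to a server".

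**The concern.** In most trials, someone who provides no follow-up data has an unknown outcome. Here non-response is what the trial measures. A participant who was sent 84 prompts and answered none has an observed completion count of 0. A rule that admits only people with a count of at least 1 selects on the primary outcome after randomisation and cuts off its bottom value.

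Two things are at stake. Average compliance is overstated, because only a zero can be removed this way. The comparison of the arms is also no longer between the groups as randomised: the arm that lost the zero looks better than it was. The excluded person's arm is not stated, so a reader cannot tell which arm that is.

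**Working it through.** **Inputs** (all from Results, except the 84 prompts, which come from Primary Outcomes and Study Implementation): 92 randomised; 91 in the final sample; 43 EMA and 48 EMA+DD; mean 64.3 and SD 14.6 of 84; 7644 possible and 5896 obtained person-moments.

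**Step 1: confirm that the exclusion reaches the compliance figures.**
- 91/92 = 98.9%, stated as 99%.
- 43 + 48 = 91, so the arm sizes are counts after the exclusion.
- 91 × 84 = 7644, exactly the stated denominator. With everyone randomised it would be 92 × 84 = 7728.

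**Step 2: overall mean with one zero added.**
- Sum = 64.3 × 91 = 5851.3.
- New mean = 5851.3/92 = 63.6, and 63.6/84 = 75.7%. The stated mean gives 64.3/84 = 76.5%.

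**Step 3: overall SD with one zero added.**
- Sum of squares about the mean on the 91 = 90 × 14.6² = 19184.4.
- Added by the zero = 64.3² × 91/92 = 4089.5.
- New SD = √((19184.4 + 4089.5)/91) = √255.8 = 16.0.

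**Step 4: effect on the arm difference.** Arm means are not reported, so assume that both equal 64.3. Adding a zero to an arm of n people lowers its mean by mean/(n + 1).
- If the person was in EMA: 64.3/44 = 1.46 surveys. The EMA+DD minus EMA difference rises by that amount.
- If the person was in EMA+DD: 64.3/49 = 1.31 surveys. The difference falls by that amount.
- For arm means anywhere from 60 to 68, the drop is 1.36 to 1.55 (EMA) or 1.22 to 1.39 (EMA+DD).

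**Step 5: compare with the precision of the trial.**
- SE of the difference on the 91 = 14.6 × √(1/43 + 1/48) = 3.07 surveys.
- 1.46/3.07 = 0.48 and 1.31/3.07 = 0.43.
- With the zero included, taking the overall SD of 16.0, the SE is about 3.34 and the ratios are 0.44 and 0.39.

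**A caution on the inputs.** The stated mean and total do not quite agree: 5896/91 = 64.8 (77.1%), not 64.3. If the total is taken as correct, adding the zero gives 5896/92 = 64.1 (76.3%). The drop is still about 0.7 of a survey, so the size of the effect does not depend on which figure is right.

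**The case against.** **The zero is not certain.** Study Implementation says the invitations were scheduled, not that they arrived. Day 1 was the first Thursday after baseline, so there was time in between to withdraw. The article does not say whether this person withdrew, could not be reached, or ignored every prompt. This objection stands as a condition: a reader might infer that the outcome is fully known as 0 of 84, but the text supports that only if the prompts were sent and consent was not withdrawn. The article reports no withdrawal or delivery failure, and absence of any response is the only ground it gives for the exclusion.

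**The remedy reaches one primary outcome of three.** This also stands. Mean response time cannot be computed for someone with no completed survey, and the article does not say whether this person returned the exit survey.

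**The arm comparison is not shown.** Results gives only pooled compliance, and an analysis plan may exist that is not available here. This stands in part. The article does call the 91 the final sample and uses 91 × 84 as the denominator, so the exclusion from the reported compliance figure is a fact; its extension to the arm comparison is likely but inferred. A reader might go further and infer that the exclusion favours the dashboard. Without the person's arm, the documents do not support that.

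**The size is modest.** One person of 92 (1.1%) is affected, the counts and the rule are disclosed, and the article describes a feasibility study that may be underpowered. This stands, and it governs the severity.

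**The order of randomisation and baseline.** A reader might infer from Participants and Trial Design that people were randomised, never finished baseline, and are missing from the 92. The documents do not support this. Study Implementation describes the mechanism in detail and puts assignment after baseline, Results lists the steps in the same order, and no such person is reported. On either account, the 21-day phase began only after baseline was completed, so nobody without a baseline survey would have had prompts scheduled.

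**Conclusion.** The point holds for the completion count. The article's rule for its final sample conditions on that outcome after randomisation and removes its lowest value, and the reported denominator confirms that the rule was applied. Correcting it moves overall compliance by less than one percentage point and the arm difference by somewhat under half a standard error, in an unknown direction.

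This rests on three assumptions: that the prompts were sent and consent was not withdrawn, that the arm means are near the pooled 64.3, and that the arm comparison uses the 91. It should be fixed because the remedy is almost free and restores the comparison as randomised. With one person affected, it is not a defect that invalidates the trial. The differing accounts of when randomisation took place are a minor, separate matter of wording.

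**What to change.** - For the completion count, define the analysis set as all 92 participants in the arms to which they were randomised. Score the non-responder 0/84, provided the records show that the prompts were sent and consent was not withdrawn.
- Report that person's arm and status (prompts delivered, unreachable, or withdrawn), whichever way the score is decided.
- Keep the 91-person analysis as a sensitivity analysis.
- State that mean response time is analysed in the 91, because it is undefined for someone with no completed survey.
- Separately, align the sentence on randomisation in Participants and Trial Design with Study Implementation and Results, after checking the order against the server's assignment record.

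The cost is one extra data row, a rerun of the completion-count comparison, one look at the server and consent records, and a few sentences of text.

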## Discussion

Results from our evaluation of the MRT will provide evidence about whether providing real-time and personalized feedback on a participant’s progress in an EMA study improves compliance across multiple metrics. MRTs have a high potential for informing the development of effective just-in-time interventions focused on higher-risk substance use behavior. Information about the use of personalized dashboards to improve compliance will be a critical finding from this study, as compliance is a critical first step toward greater overall study engagement. Evaluating the effect of receiving a DD on speed of completing that particular survey will also be useful, as it reflects a state of investment or energy and cognitive energies, key components of engagement [16].

Further, REDCap and similar data collection tools are ubiquitous in most university settings. Thus, our automated approach could be deployed at many institutions with existing technology. This approach circumvents the often tedious or slow process of gaining approval for use of a third-party service to deploy such studies. Although REDCap does not natively support EMA data collection, there are relatively straightforward workarounds to automate a tailored process such as in this study. Because of the nearly universal adoption of these software packages, a wealth of information including community forums also exists online to troubleshoot issues and develop new techniques.

This study necessitated a specialized system to implement the generation of the DD based on real-time information of the participant. Through a collaboration with the institution’s survey research center, expert staff were able to connect the REDCap system to a server in which custom code was used to determine the timing of deployment, calculate data for inclusion, and generate the DD for each individual at appropriate times.

This feasibility study was limited in sample size and thus may be underpowered to evaluate the effectiveness of the DD. Further, generalizability to the broader population of young adults may be limited given that all participants were currently attending college at a large, predominantly White, public university in the Northeast region of the United States. Additionally, the system designed for this study was specific for iPhone users; additional modifications would be necessary to adapt the study for Android phone users.

Overall, this study will inform whether a simple, automated DD that presents study compliance and incentives earned to date could improve ongoing compliance and overall engagement in intensive longitudinal studies. Future research could expand this scope by varying the frequency of presenting a DD (including providing one at every assessment point) and adding additional information to the graphical presentation of data. Additionally, real-time data such as biofeedback data from wearable devices could be integrated in future studies to further personalize messaging. For example, a heart rate monitor could be used to tailor messaging that corresponds to a DD, such as “Your heart rate was really high this afternoon. You said you like to meditate—might be a good idea to try it now.” Such personalization could help researchers to better understand and improve on the effects of providing a personalized DD and use it to trigger tailored intervention content. Alternatively, future studies might take into consideration relevant, passively detected contextual features such as current weather to determine whether they moderate the effect of receiving a DD.

## Abbreviations

DD: data dashboard
EMA: ecological momentary assessment
MRT: microrandomized trial
REDCap: Research Electronic Data Capture
THC: Δ-8-tetrahydrocannabinol
